### Analyses

The focus of phase one (the open pilot study) is acceptability and feasibility of the intervention in routine primary care. Therefore, the proportion of participating primary healthcare professionals who login to the online training intervention programme and complete it within the required time period (four weeks) will be assessed. The proportion of participating patients who attend/fail to attend MaMT2D appointments will also be assessed. Finally, completion rates of questionnaires for both primary healthcare professionals and patients will be assessed throughout the open pilot study. Where suggestions for improvement are made by primary healthcare professionals and patients during semi-structured interviews, these will be discussed by the research team and implemented where appropriate/feasible. Analyses of these data will be descriptive, with 95% CIs reported where appropriate. Analyses of qualitative data collected using the Theoretical Domains Framework will identify domain specific beliefs likely to positively or negatively influence acceptability and feasibility of MaMT2D in the primary care setting.

### Phase two: Movement as Medicine for Type 2 Diabetes: Pilot randomised controlled trial

#### Objectives

The aim is to assess acceptability, feasibility and fidelity of MaMT2D in the primary care setting over a 12-month period.

The primary objectives are:

1. To demonstrate that recruitment of primary care practices and patients to the trial is feasible; to determine the length of time required to complete practice and patient recruitment; and to assess eligibility, recruitment, retention and adherence rates and willingness to be randomised.

2. To assess whether intervention components are delivered faithfully and consistently in accordance with the protocol over a 12-month period.

3. To conduct a qualitative process evaluation to identify enabling factors and barriers to effective implementation of MaMT2D in primary care.

The secondary objectives are:

1. To estimate the variability of objectively assessed PA behaviour, diabetes related knowledge, attitudes/beliefs, self-efficacy for being physically active and health related quality of life, HbA1c, blood pressure, waist circumference and body mass index in patients by generating interval estimates of the mean difference between groups for each outcome measure.

2. To estimate the variability both between subjects and between clusters of PA related knowledge, self-reported PA behaviour, attitudes/beliefs, self-efficacy for delivering a behavioural intervention and fidelity of specific behaviour change techniques and behaviour change counselling skills in the context of diabetes management in primary healthcare professionals. Interval estimates of the mean difference between groups for each outcome measure will be generated.

Estimates of variability will include the standard deviation, range and interquartile range for each of the study outcomes. The estimates of standard deviation will be used to generate 95% CIs for mean scores in each group and the difference in group means.

## Methods/Design

The second phase will involve a two-arm parallel group cluster RCT (practices will be the unit of randomisation) to assess acceptability, feasibility and fidelity of the intervention and study procedures over a 12-month period.

### Sample size

A total of 200 patients will be recruited from up to 20 primary care practices in the County Durham and Darlington area of North East England. The final number of practices will be identified following completion of phase one (open pilot) where an assessment of practice recruitment and retention rates will be conducted, with reference to practice list size (with three cut-off points: <3,280; ≥3,280 to 5,989; ≥5,990 to 10,453; and >10,454); the number of patients fulfilling the eligibility criteria and the number of patients recruited per practice. Up to 10 practices will be randomised to MaMT2D and a further 10 to usual clinical care. Although the trial is not powered for a definitive analysis, exploratory analyses examining between group differences will be reported based on a calculation of physical activity behaviour and HbA1c. The data generated from the pilot RCT including an estimate of the intra-cluster correlation co-efficient [47] will facilitate a power calculation to inform a definitive RCT if acceptability, feasibility and fidelity are demonstrated.

### Eligibility criteria for primary care practices and patients

Eligibility criteria for primary healthcare practices and patients will be identical to those used in phase one.

### Recruitment procedures

Figure 1 presented earlier provides an overview of practice and patient recruitment.

Recruitment procedures will be identical to those used during the open pilot study and primary healthcare professionals from each participating practice will be required to provide informed written consent prior to randomisation.

### Pilot RCT trial arms

There are two arms to the trial, (1) the control group: usual clinical care; and (2) the intervention group: MaMT2D. Despite the known benefits of PA on glycaemic control, there remains a lack of evidence-based interventions designed to increase PA in people with Type 2 diabetes. Furthermore, it remains unclear what the optimal strategies are to increase PA behaviour in people with Type 2 diabetes and whether a programme such as MaMT2D will be acceptable and feasible in the primary care setting.

Figure 1 provides an overview of planned recruitment numbers, timing of the intervention sessions and outcome measures.

### Usual clinical care (control group)

Patients will be asked to attend four face-to-face appointments (baseline, one, six and twelve months). During the initial appointment they will be given a Diabetes UK leaflet (‘Keeping active: an essential part of managing diabetes’) [48]. No further information or advice will be provided to patients about PA over and above usual clinical care.

At the three-month follow-up all participating patients will receive a telephone call from a primary healthcare professional at their practice to ask if they have any questions regarding their diabetes management and participation in the study. At the same time patients will be mailed a postcard by the research team thanking them for continuing to take part in the study.

### Movement as Medicine for Type 2 Diabetes (the intervention)

#### Healthcare professional online training intervention programme

Primary healthcare professionals employed by practices randomised to the intervention arm of the study will complete the online training intervention programme component of MaMT2D (optimised following the open pilot during phase one). The procedure for access and content is described previously for the open pilot study.

Primary healthcare practices randomised to deliver usual clinical care will be offered access to the online training intervention programme following completion of the pilot RCT.

### Primary healthcare professional-led intervention

Patients will be asked to attend four face-to-face appointments (baseline, one, six and twelve months). During these appointments they will be given a Diabetes UK leaflet (also issued to the control group) and will receive the optimised version of the primary healthcare professional-led intervention and associated materials informed by findings of the open pilot in phase one. Intervention components are described previously for the open pilot study.

### Primary outcome measures

1. An assessment of primary care practices and patient’s willingness to take part in the trial will be conducted by examining the proportion of practices and patients that were both eligible and asked to participate against those who actually agreed to participate.

2. The patient identification procedure will be examined to determine whether identification of eligible patients from practice lists was feasible, rates of eligibility and reasons for ineligibility.

3. Acceptability of the study design will be measured by the number of primary care practices and patients who take part and remain in the trial (that is, appointment attendance and intervention, data and study completion rates) and reasons for drop-out, where provided will be examined. In a situation where a patient does not attend an appointment but contributes data at a specific data collection time point, this information will be recorded.

4. Primary care practice and patient recruitment rates will be measured by the number who consent to be randomised divided by the number eligible to be randomised and the number taking part in the trial divided by the length of the recruitment period. The practice recruitment period begins when the first round of practice invitations are mailed out and ends when the last practice recruited is randomised. Patient recruitment begins when the first group of eligible patients is mailed their invitation letter and ends when the last patient recruited provides informed written consent.

5. Willingness to take part in video recordings of consultations, semi-structured interviews and focus group discussions will be assessed in both the intervention and control groups.

6. Adherence to the study protocol (fidelity assessment) and barriers/facilitators to effective implementation of MaMT2D in the primary care setting will be assessed throughout the trial period. A proportion of consultations will be video recorded to assess adherence to intervention components; and data collection completion rates will be monitored and recorded at each data collection time point. Semi-structured interviews with participating primary healthcare professionals and patients will be conducted to identify barriers and enabling factors to implementation of the intervention in routine primary care.

### Secondary outcome measures

1. Estimates of variability will be calculated for objectively assessed PA behaviour and diabetes-related knowledge, attitudes/beliefs, self-efficacy for being physically active, health related quality of life, HbA1c, blood pressure, waist circumference and body mass index in patients at each data collection time point. Estimates of variability will include the standard deviation, range and interquartile range for each study outcome. Estimates of standard deviation will be based on an appropriate multilevel model (subjects nested within practices); the variance will be partitioned into between subject and between practice components.

2. Estimates of variability will be calculated for fidelity of specific behaviour change techniques, behaviour change counselling skills (in the context of diabetes management) and PA related knowledge, self-reported PA behaviour, attitudes/beliefs and self-efficacy for delivering a behavioural intervention.

3. A qualitative process evaluation will be undertaken concurrently to assess barriers and facilitators to effective implementation of the intervention into routine primary care. A refined and optimised version of both components of MaMT2D (online training intervention programme for primary healthcare professionals and the range of printed materials, DVD and pedometer (SW200, Yamax Corporation, Tokyo, Japan) for patients (as part of the primary healthcare professional-led intervention) will be compared with usual clinical care. Assessment of all outcomes will inform future work (for example, a definitive RCT).

### Patient outcome measures

PA behaviour will be measured objectively using a blinded (that is, no data visible to patients) wrist worn tri-axial accelerometer (GENEActiv, ActivInsights Ltd, Kimbolton, UK) for seven continuous days at each data collection time point. Clinical outcome measures, comprising glycaemic control (HbA1c), diastolic and systolic blood pressure (mmHg), waist circumference (cm) and body mass index (kg/m^2^), will be measured and recorded by primary healthcare professionals during review appointments. Self-reported PA (International Physical Activity Questionnaire (IPAQ)) [49]; diabetes-related knowledge (Audit of Diabetes Knowledge (ADKnowl)) [50]; behavioural intentions, subjective norms and attitudes/beliefs about PA for the management of diabetes (Physical Activity Questionnaire for Diabetic Patients (PAQ-DP)) [51]; PA-related self-efficacy [52]; and health-related quality of life (Audit of Diabetes Dependent Quality of Life (ADDQoL)) [53] will be measured by self-report postal questionnaire. Each outcome will be assessed at baseline, one, six and twelve-month follow up. Background information will be collected from patients on age, gender, employment status, length of time since diagnosis of Type 2 diabetes and method of diabetes control (that is, diet, oral medication).

### Healthcare professional outcome measures

Change in consultation behaviour involving utilisation of selected behaviour change techniques and behaviour change counselling techniques will be assessed subjectively using a questionnaire specifically developed for the purpose of this study. Objective assessments will be made by video recording a sub-sample of primary healthcare professionals in practice. Self-reported diabetes and PA-related knowledge; behavioural intentions, subjective norms, attitudes/beliefs about PA as a management option for Type 2 diabetes (adapted PAQ-DP) [51]; self-efficacy for delivering a behaviour change intervention [52]; and PA behaviour (IPAQ) [49] will be assessed by online questionnaire at each data collection time point (baseline, one, six and twelve months follow up). Background information will be collected about current job title and role, length of time in current role, details of any previous training undertaken in the area of health behaviour change (for example, behaviour change counselling and motivational interviewing), diabetes and PA for the management of Type 2 diabetes.

### Treatment fidelity assessment

A sub-sample (20% to 40%) of consultations will be video recorded to assess fidelity of primary healthcare professionals use of specific behaviour change techniques and behaviour change counselling techniques within MaMT2D consultations (and usual care consultations) with patients. Each intervention component will be coded as either ‘present’ or ‘absent ‘and an assessment will be made on the extent to which it was utilised (that is, how closely delivery meets pre-specified criteria of behaviour change techniques (BCTs) and intervention components). The Behaviour Change Counselling Index (BECCI) [54] will be used to assess primary healthcare professional’s use of behaviour change counselling skills to enhance patient-centeredness of consultations. A sub-sample of video recordings will be double coded by a second coder and any discrepancies will be resolved by a third coder. All coders will have expertise in theory-linked BCTs, including experience using the 40-item taxonomy [55] used to define BCTs and behaviour change counselling techniques included in MaMT2D. This assessment will enable quantification of primary healthcare professional and patient interactions, to provide insights into the therapeutic relationship, as well as allow an assessment to be made as to whether this relationship translates into actual PA behaviour change. The outcome of these analyses obtained during the pilot RCT will help to understand the nature of the interaction during MaMT2D consultations and usual clinical care, and to identify any potential barriers and facilitators to effective implementation of the intervention in routine primary care. Assessment of treatment fidelity will help determine whether any estimated differences detected in objectively assessed PA behaviour between the intervention and control group patients can be attributed to any changes in consultation behaviour of participating primary healthcare professionals (influenced by the online training intervention programme) [42,56].

To maximise treatment fidelity a number of strategies will be used.

### Treatment fidelity strategies for design of the study

Both intervention and control group patients will receive the same ‘treatment dose’ (that is, the same number of contacts from primary healthcare professionals and the research team). To plan for implementation setbacks a minimum of two primary healthcare professionals will be recruited (and trained in the intervention arm of the study) from each primary care practice. By utilising treatment fidelity strategies related to study design, the study aims and objectives can be adequately tested.

### Treatment fidelity strategies for monitoring and improving provider training

A standardised online training intervention programme will be provided to ensure all primary healthcare professionals in the intervention arm of the study receive access to the same training content. Where primary healthcare professionals do not adhere sufficiently to delivery of pre-selected behaviour change techniques and behaviour change counselling skills, the research team will explore possible reasons for this and changes to the intervention will be made as appropriate during the open pilot study. Video recordings of consultations will be made throughout phases one and two to assess skill acquisition, utilisation and treatment fidelity.

### Treatment fidelity strategies for monitoring and improving receipt of the intervention

A qualitative process evaluation and treatment fidelity assessment will be conducted throughout phases one and two to assess primary healthcare professional performance on delivery of specific behaviour change techniques and behaviour change counselling skills.

### Qualitative process evaluation

Interviews will be carried out with a purposive sample of primary healthcare professionals and patients during phases one and two of the study. Interview topic guides will be developed using the TDF [38]. The outcome of interviews will help to optimise the intervention, and streamline study processes and procedures during phase one and to obtain an in-depth understanding of barriers and facilitators to successful implementation during phase two. Interviews will be audio recorded, transcribed and data will be analysed using thematic analysis. A proportion of transcripts will be analysed by a second researcher.

### Data collection, storage and security

Data collected via audio recorders, video recorders and accelerometers will be saved to a password protected server in the Institute of Cellular Medicine (ICM) at Newcastle University. These data will be accessed only by members of the research team. Once all data have been uploaded to the server they will be securely deleted from the recording devices. Patient questionnaire data will be anonymised and stored in locked filing cabinets in the ICM.

### Randomisation and concealment of allocation

Practice recruitment will be carried out in two stages. Practices will be randomly allocated to the intervention or usual clinical care group after each recruitment stage and following receipt of informed written consent from participating primary healthcare professionals. Consent will be obtained by a member of the research team who is blind to details of randomisation sequencing and concealment. Practices will be allocated to one of four strata based on list size with three cut-off points: <3,280; ≥3,280 to 5,989; ≥5,990 to 10,453; and >10454 (thresholds based on quartiles of distribution of list size across all practices in the County Durham & Darlington area of North East England) and will be randomised independently within strata using random permuted blocks. The blocks will be generated using a subroutine that utilises the ‘rand()’ function built into the programming language awk implemented on the central Linux system at Newcastle University. The size of blocks will be concealed until the end of recruitment.

### Blinding

It is inherently difficult to blind primary healthcare professionals and patients in behavioural interventions with the nature of usual clinical care for diabetes being so well defined. Therefore, blinding of participants will not be possible. Due to pragmatic reasons researchers will not be blinded to group allocation of participating practices; however, the statistical analyses will be performed by a statistician blind to the treatment allocation of participating primary healthcare professionals and patients.

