This protocol describes a two-phase process that will be used to develop and evaluate MaMT2D. Phase one is an open pilot study that will assess the acceptability, feasibility and fidelity of delivery of MaMT2D and will provide opportunities for intervention optimisation and refinement of study processes and procedures. Phase two is an external pilot cluster randomised controlled trial (RCT) that will assess acceptability, feasibility, and fidelity of MaMT2D (informed by any necessary optimisation identified in phase one) over a 12 month period. A qualitative process evaluation and treatment fidelity assessment will be carried out throughout the trial period, to identify any barriers and facilitators to implementation as well as adherence to the study protocol by primary healthcare professionals and patients. The pilot RCT will be conducted and reported in accordance with the Consolidated Standards of Reporting Trials (CONSORT) [34] and the Standard Protocol Items: Recommendations for Interventional Trials (SPIRIT) guidelines [See Additional file 1: SPIRIT Checklist) [35].

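### Fidelity in both arms is rated from video by a research team not blinded to allocation, so coder expectation can bias the between-arm fidelity estimate

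*Protocol article*

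**What the plan says.** All references are to the protocol article.

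- **Role of fidelity.** Primary objective 2 of phase two is "To assess whether intervention components are delivered faithfully and consistently in accordance with the protocol over a 12-month period". Under Primary outcome measures, item 6 says "A proportion of consultations will be video recorded to assess adherence to intervention components". Secondary objective 2 lists fidelity of specific techniques and counselling skills among its measures, and adds: "Interval estimates of the mean difference between groups for each outcome measure will be generated".
- **How it is rated.** Under Treatment fidelity assessment, each component is coded as present or absent, and "an assessment will be made on the extent to which it was utilised". The Behaviour Change Counselling Index (BECCI) is also scored. Ratings are made "within MaMT2D consultations (and usual care consultations) with patients".
- **Who rates.** Data collection, storage and security restricts access to the video data to the research team. The Blinding section says "Due to pragmatic reasons researchers will not be blinded to group allocation of participating practices", and only the statistician is blinded.
- **Safeguards.** "A sub-sample of video recordings will be double coded by a second coder and any discrepancies will be resolved by a third coder". Ratings are made against pre-specified criteria, and coders must have expertise in behaviour change techniques and experience with a 40-item taxonomy.
- **Timing.** The Background says that a "treatment fidelity assessment will be carried out throughout the trial period". The article gives no order of coding, no masking of coders to visit and no check for drift.

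**The concern.** Whether a component was present, how far it was used, and how a consultation scores on the BECCI all depend on the coder's judgement. A coder who knows that a practice was trained may credit an ambiguous exchange as a technique, and may read the same exchange in a usual-care practice as ordinary conversation.

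Two stated uses of the data are exposed. One is the interval estimate of the between-arm difference in fidelity under secondary objective 2. The other, under Treatment fidelity assessment, is the use of fidelity to judge whether differences in physical activity can be attributed to changed consultation behaviour. The result also has consequences: under Sample size for phase two, the pilot data inform a definitive trial if acceptability, feasibility and fidelity are demonstrated.

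A second, weaker risk concerns consistency over 12 months, which has to be read across visits. If recordings happened to be coded in visit order, a change in the coders' standard would look like a change in delivery.

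**Working it through.** **Do the coders know the arm?** No sentence says so directly; it follows from two sections. Only the research team can access the videos, and researchers are not blinded to practice allocation. The coders therefore know, or can know, the arm. The blinded statistician enters only after the ratings exist.

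**Number of recordings.** Inputs from the article are 200 patients, four appointments each, and 20% to 40% of consultations recorded. Assuming full attendance and an equal split between arms and visits:
- Consultations: 200 × 4 = 800
- Recorded: 800 × 0.20 = 160 to 800 × 0.40 = 320
- Per arm: 80 to 160
- Per arm per visit: 20 to 40

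**Between-arm contrast (illustration).** Take one component that is truly present at rate p in both arms. The observed rate is p × Se + (1 − p) × (1 − Sp), where Se and Sp are the coder's sensitivity and specificity, both assumed to be 0.85. Let the coder be more lenient in one arm: Se rises by s and Sp falls by s. The spurious difference is then p × s + (1 − p) × s = s, whatever the true rate. At p = 0.5 and s = 0.10, the observed rates are 0.5 × 0.85 + 0.5 × 0.15 = 0.50 and 0.5 × 0.95 + 0.5 × 0.25 = 0.60.

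The table gives the chance of a nominally significant arm difference when there is no true difference (two-sided 5% test of two proportions, reference rate 50%, clustering ignored):

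| Assumed leniency shift | 80 per arm | 160 per arm |
|---|---|---|
| 5 points | 9% | 14% |
| 10 points | 24% | 44% |
| 15 points | 48% | 78% |

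The 95% half-width for the difference is 1.96 × √(0.5/80) = 15.5 points, or 1.96 × √(0.5/160) = 11.0 points. More recordings narrow the interval but leave the bias as it is, so the chance of a false difference rises.

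**Change between visits (illustration).** The 14 techniques come from the list in the Background. Mean fidelity of 60% and a within-consultation item correlation r of 0.1 to 0.3 are assumptions.
- Variance of one consultation's mean: 0.6 × 0.4 × (1 + 13r)/14, which is 0.0394 at r = 0.1 and 0.0840 at r = 0.3
- SE for one visit: √(0.0394/40) = 3.1 points to √(0.0840/20) = 6.5 points
- SE of a change between two visits: multiply by √2, giving 4.4 to 9.2 points
- An assumed coder drift of 5 to 10 points, relative to that SE: 5/9.2 = 0.5 to 10/4.4 = 2.3

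This treats all 14 techniques as applicable at every visit, although the article accepts that some are appropriately absent. It also treats consultations as independent, although they are nested in professionals and practices. Allowing for either would generally widen the SE and lower the ratio.

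**The case against.** Several points on the other side have force.

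- **Masking to visit and coding order.** A reader might infer that coders see the visit and work through recordings in visit order, so that drift will pass for a trend. The article does not say this. Assessment throughout the trial fixes when material is gathered, not the order in which it is coded, and a condensed article may leave coding procedure to the full protocol. This stands: drift is a possible risk only.
- **Primary versus secondary purpose.** A reader might infer that unblinded coding undermines primary objective 2 through the arm contrast. That objective asks whether the intervention's components are delivered as the protocol intends; the between-arm estimate belongs to secondary objective 2. This also stands.
- **Safeguards.** Double coding is not the only one. There are also pre-specified criteria, a named index, experienced coders, and coding and double coding already used in the open pilot. These limit individual error. They do not remove an expectation shared by coders who all know the arm, and the third coder settles only disagreements within the double-coded sub-sample.
- **Monitoring.** The Discussion and the section on monitoring and improving receipt of the intervention give fidelity assessment a role during the trial, which coding only at the end would forfeit. This stands, and the fix must allow for it. However, the section on provider training places changes to the intervention in the open pilot, so no stated decision within the RCT needs the outcome scores early.
- **Masking is limited anyway.** The toolkit on screen will often reveal the arm, and reviews of earlier progress will often reveal the visit. Removing labels helps most where little toolkit material appears; random order helps in either case.
- **Disclosure.** The article states openly, with a pragmatic reason, that researchers are unblinded, and the phase two analyses are descriptive. Nothing is contradicted or miscalculated.

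**Conclusion.** The concern holds for the arm contrast. Fidelity is a judgement rating made in both arms by a team stated to be unblinded, and no stated safeguard removes a shared expectation. What is exposed is the between-arm fidelity estimate and the use of fidelity to explain physical activity differences.

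The size is unknown because the documents give no figure for coder bias. The 24% to 44% chance of a nominally significant difference rests on an assumed 10-point leniency shift, a 50% reference rate and no clustering. Drift across visits is unproven; 5 to 10 points, if it occurred, would be about 0.5 to 2.3 times the SE of a between-visit change, so it could be well within noise or clearly visible. This is a worthwhile low-cost improvement to a pilot, not an error that invalidates it.

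**What to change.** For the RCT outcome ratings:
1. Remove practice, arm and visit labels from the recordings given to coders.
2. Once the last recording is in, code them in one random order across arms and visits.
3. Draw the double-coded sub-sample in equal numbers from each visit.
4. Report agreement before discrepancies are resolved, by visit.
5. Keep any monitoring of delivery during the trial separate, and do not carry its scores into the outcome data.
6. State in the report that masking was partial because toolkit use and session content can reveal arm or visit.

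The cost is file renaming and a random coding list, with no extra recordings. A recording also used for monitoring would need a separate outcome rating, which adds some coding time. Final fidelity scores would come later. Random order breaks the link between drift and visit even where masking fails, but it does not remove an expectation formed when the arm is visible on screen.
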